#### Data management

Data is either saved automatically in E-prime data files (for the interpretation bias measures) or the experimenters enter data manually into SPSS data files (for all other measures). We assure the quality of data entry by random checking of the data entered. After each day of testing we will back-up the data on the first author’s personal KU Leuven network drive which the KU Leuven IT department in turn automatically backs-up daily.

There is no data monitoring committee due to the characteristics of the current study: a nonclinical participant group, tested for a short period of time with intervention(s) that have not been reported previously to harm participants [53]. There are no interim analyses and stopping guidelines planned.

Study data is only accessible by the researchers involved in the trial. Feedback on how an individual participant results is not possible; however, we plan to communicate summarized general results to parents who are interested. Parents are informed about this option in the informed consent.

#### Data analysis

For all analyses, we consider effects for which *p* values < .05 as statistically significant. We assess baseline comparability of the groups using descriptive statistics (gender, age). We use one-way analyses of variance (ANOVAs) to assess pre-intervention differences between the four intervention conditions on the outcome measures. Data that is missing completely at random will be calculated using Expectation Maximization.

The aim of the present study is to explore the effectiveness of CBM training, OT and both interventions combined on trust in maternal support on three levels: trust-related interpretation bias; self-reported trust; and mother-child interactional behavior. To assess the main and interaction effects of the interventions on change scores on these outcome measures, we will perform a two-way ANOVA with training condition (CBM versus neutral) and nasal spray condition (OT versus PL) as between-subject variables. Only in case of the measure of interpretation speed of secure and insecure scenario resolutions, we add the within-subject factor probe valence (secure versus insecure). Additionally, in order to check whether the dose of intranasal OT that is administered affects intervention effects on change scores on the outcome measures, we plan to run a two-way ANOVA in the OT intervention condition with training condition (CBM versus neutral) and OT dose (12 IU versus 24 IU) as between-subject variables and children’s weight as covariate.

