The pharmacy of the University Hospital of Heidelberg, Germany, carried out the randomization of the nasal sprays using RITA software version 1.30 [48]. They stratified randomization by training condition and used permuted blocks within strata [49]. The bottles containing OT nasal spray and PL look identical and the pharmacy of the University Hospital of Heidelberg numbered all nasal sprays. For each nasal spray number, a sealed envelope contains a piece of paper that connects the spray number to one of the interventions. Additionally, all envelopes contain a black piece of paper to prevent visibility of intervention allocation without opening the envelope. We assign the numbered nasal sprays to consecutive participants in sequential order, with training condition alternated between participants. Since both interventions are placebo-controlled, participants are blind to the intervention condition that they are in. Experimenters are aware of the training condition, but blind to the nasal spray condition. To conceal intervention allocation and maintain blinding, we do not open the envelopes until after data collection is finished. Only in case of severe adverse events, it is possible to open a sealed emergency unblinding envelope to unblind the medication for a given participant. We assess children’s awareness of the experimental condition (i.e., both the training and the nasal spray condition) that they are in at the end of the procedure. Furthermore, we assess experimenter’s and mother’s awareness of the nasal spray condition at the end of the procedure and 24 h after the procedure, respectively. The mother-child dyad is given a participant number that we use on all data documents. A separate password-protected document links participant names to participant numbers. In case of severe adverse events after nasal spray administration, the procedure can be discontinued. Moreover, mother and child can withdraw from the study at any time without giving a reason.

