#### Sample size

The current study is powered to test the main hypotheses; that is, to identify a difference (moderate effect size, *f* = 0.30) in outcome measures between the four treatment conditions. Since this was the first study to combine CBM and OT interventions to investigate their main and interaction effects on trust-related outcome measures, there were no effect sizes from comparable studies that we could use to calculate the sample size needed. However, relevant prior studies point to the fact that a moderate effect size might be expected. Specifically, previous studies using the same CBM training obtained effect sizes ranging from *f* = 0.29 to *f* = 0.48 for trust and trust-related outcome measures [23, 79]. Additionally, a meta-analysis of effects of OT administration to in-group trust showed an effect size *f* = 0.24, with an effect size *f* = 0.32 for studies with a between-subject design such as the current study [33].

We used G*power 3.1 [80] to computed the required sample size for an ANOVA test for main effects and interactions. Input parameters were: a moderate effect size, *f* = 0.30; alpha = .05, two-tailed; power = 0.80; numerator *df* = 1; number of groups = 4. G*power revealed that a sample size of 90 participants is required to have a power of 0.80 to identify a moderate effect between the four treatment conditions (critical *F* = 3.95). We plan to recruit 100 participants in total (25 in each intervention condition), yielding an actual power of 0.84 (critical *F* = 3.94).

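### Filling missing outcome scores by Expectation Maximization and then running an ordinary ANOVA distorts either the type I error or the effect estimate, depending on an EM set-up the article does not state; observed cases would do better

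*Protocol article*

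**What the plan says.** The Data analysis section of the protocol article gives one sentence on missing data: "Data that is missing completely at random will be calculated using Expectation Maximization". For the change scores it then says "we will perform a two-way ANOVA with training condition (CBM versus neutral) and nasal spray condition (OT versus PL) as between-subject variables". It does not mention repeated imputation, residual draws, pooling or any adjustment of the variance. It does not list the variables in the EM model, and it does not say whether whole scores or single items are filled.

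Whole post-intervention scores can be lost. The Study design section says "In case of severe adverse events after nasal spray administration, the procedure can be discontinued", and it lets mother and child withdraw at any time. No expected missing rate is given.

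The Sample size section powers the trial for main effects and interaction: "Input parameters were: a moderate effect size, *f* = 0.30", "alpha = .05, two-tailed; power = 0.80", "number of groups = 4". It concludes that "a sample size of 90 participants is required to have a power of 0.80" and plans to recruit 100, with 25 per condition.

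**The concern.** An EM fill without residual noise puts a conditional mean where a measurement should be. An ordinary ANOVA then counts that value as a full observation with no uncertainty of its own. There are two ways to set up the fill, and each has its own cost.

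- **Conditions in the EM model.** The group difference is preserved, but the residual variance is understated and the sample size overstated. Tests reject too often against the planned .05 threshold.
- **Conditions left out.** Filled values carry no group difference, so the estimated effect shrinks towards zero.

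Under the mechanism the sentence names, missing completely at random (MCAR), leaving the gaps alone already gives an unbiased estimate and a correct standard error. The stated rule can therefore do worse than no imputation in the case it covers.

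**Working it through.** **Inputs from the article.** 100 children, 25 per condition; f = 0.30, which for a two-level main effect is d = 2f = 0.60 SD of the change score; alpha .05.

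**Assumed inputs.** 2%, 5%, 10% or 20% of post-intervention scores missing completely at random; pre-post correlation ρ of 0.5 to 0.8.

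**1. The plan's own figures.** Noncentral F with λ = N f², df 1 and N − 4.
- N = 90: λ = 90 × 0.09 = 8.1, critical F 3.95, power 0.803.
- N = 100: λ = 9.0, critical F 3.94, power 0.844.

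Both agree with the article (90 for power 0.80; 0.84 at 100).

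**2. Observed cases only.** The same formula gives power 0.836 at n = 98, 0.825 at 95, 0.803 at 90 and 0.755 at 80. In simulation (6,000 runs per setting, ρ = 0.5 and 0.8), type I error was 4.8-5.3% and a true 0.60 was estimated as 0.59-0.60.

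**3. EM fill without the conditions.** A share m of each group is filled with values that carry no group difference, so the expected estimate is 0.60 × (1 − m): 0.588, 0.570, 0.540 and 0.480 for m = 2%, 5%, 10% and 20%. Simulation gave about 0.59, 0.57, 0.54 and 0.48, with type I error of 4.6-5.4%. The smaller reported SE (0.192 against 0.211 for observed cases at 10%, ρ = 0.5) buys no power. At 20% missing, power was 0.73-0.75, against 0.75-0.76 for observed cases.

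**4. EM fill with the conditions.** Take ρ = 0.5 and unit SD before and after. Change then has variance 2 − 2ρ = 1, of which (1 − ρ)² = 0.25 is explained by the pre-score and 1 − ρ² = 0.75 is not. Filled values carry only the 0.25. With 50 children per factor level, the full-data SE is 2/√100 = 0.2, and approximately:
- reported SE = 0.2 × √(1 − 0.75m)
- true SE = 0.2 × √(0.25 + 0.75/(1 − m))
- type I error = 2Φ(−1.96 × reported/true)

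At m = 10%: 0.192/0.208 = 0.92, giving 7.0%. At m = 20%: 0.184/0.218 = 0.85, giving 9.7%. Simulation at ρ = 0.5 gave ratios of 0.91 and 0.835, and type I error of 7.0% and 9.9%.

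The table collects simulations over ρ = 0.5, 0.6 and 0.8 (3,000 to 6,000 runs per setting; Monte Carlo error about 0.3 points at 6,000 runs, more with fewer).

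| Post scores missing | Conditions in EM: type I error | Conditions not in EM: estimate of a true 0.60 |
|---|---|---|
| 2% | 5.0-5.7% | 0.59 |
| 5% | 5.5-6.7% | 0.57 |
| 10% | 7-8% | 0.54 |
| 20% | 10-12% | 0.48 |

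**5. Single items filled, conditions in the model.** For a 10-item scale (assumed item intraclass correlation 0.3, ρ = 0.6, 2,500 runs), type I error was 4.8%, 5.6% and 5.7% with 2%, 5% and 10% of items missing (Monte Carlo error about 0.4 points). The reported SE was 0.97-0.99 of the true SE.

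**The case against.** The strongest case against the point is that little may be missing. All efficacy outcomes are collected in one session of 120 to 150 minutes, the interpretation-bias data are saved automatically, and the only later contact is the 24-hour side-effects call. Trust is a mean of 10 items and each recognition-task score a mean over seven scenarios, so the sentence may be meant for skipped items. At 2% of scores missing, or with items filled, the calculations above show almost no harm. This stands, and it limits the size of the point. It does not rescue the rule for a lost post-intervention score, which the wording also covers.

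A reader might infer more than the article supports:

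- *That the article states a single fill analysed as observed data.* It does not use those words. This is the natural reading, because nothing about pooling or variance follows, but it is a reading.
- *That standard errors are too small in every case.* This holds only with the conditions in the EM model. Without them, the harm is attenuation at a nominal error rate.
- *That data not missing completely at random have no rule.* The article names none, but a statistical analysis plan not shown here may do so. Missingness that depends only on treatment group also leaves observed cases unbiased.
- *That imputation has no use under MCAR.* It is not needed to avoid bias, but it can recover some precision.
- *That the change-score ANOVA itself must go.* That is a separate choice of estimator. The defect here lies in the fill.

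**Conclusion.** The point holds in conditional form. The article fixes a method that, if applied once to whole outcome scores, gives worse inference than the planned ANOVA on observed cases. With 10% missing, the price is either a type I error of about 7-8% or an effect of 0.54 instead of 0.60. With 20%, it is 10-12% or 0.48. The two harms belong to alternative set-ups, and the article does not say which applies. At about 2% missing, or with item-level filling, the point is negligible in practice.

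The conclusion rests on assumed missing rates and pre-post correlations, on MCAR, and on a fill without residual noise. The sample-size figures are correct and are not affected.

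**What to change.** Replace the EM sentence. Outcome scores that are missing are not filled, and the planned two-way ANOVA is run on children with the scores it needs. If EM is meant only for skipped questionnaire items, say so and name the variables in the model.

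Add a second sentence for missingness that is more than trivial or may depend on the child. Either fit a likelihood-based model to all observed pre and post scores with training, spray and their interaction, or use multiple imputation that includes those three terms, combined by Rubin's rules.

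The cost is two sentences, standard software, a little more analysis work and no new data. The interval is slightly wider: with 10% missing, the observed-case SE is about 1/√0.9 = 1.05 times the full-data SE. The 10 children recruited above the required 90 already cover that loss.

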### Measures

#### Outcome measures

An overview of outcome measures is presented in Table 2.

**Table 2 Tab2:** Outcome measures

Domain	Specific measurement	Metric	Method of aggregation	Time point		
				Baseline	Training	Post-intervention
Interpretation bias	Interpretation speed of secure and insecure scenario resolutions	Difference between secure and insecure resolutions	Mean reaction time to secure and insecure probes		x	
	Secure interpretation bias	Change from pre-intervention to post-intervention recognition task	Mean rating of secure interpretations	x		x
	Insecure interpretation bias	Change from pre-intervention to post-intervention recognition task	Mean rating of insecure interpretations	x		x
Trust	PIML Trust subscale	Change from pre-intervention to post-intervention	Mean rating of trust items	x		x
Child’s attachment-related behavior	Observation of the quality of the approach of child towards mother during a puzzle task with the MCAM scoring scales	Change from pre-intervention to post-intervention	Frequency of child behaviors	x		x
Mother-child interactional coherence	Observation of positive parent behavior and positive child behavior (with the MCAM scales) during a puzzle task	Change from pre-intervention to post-intervention	Jaccard Index indicating the occurrence of parent behavior at time point t − 1 and child behavior at time point t and vice versa (i.e., indicating the occurrence of child behavior at time point t − 1 and parent behavior at time point t)	x		x

*PIML* People In My Life; *MCAM* Middle Childhood Attachment Micro-observation system

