##### Change in trust

We measure trust in mother with the Trust subscale of the People In My Life Questionnaire (PIML) [57]. This subscale contains 10 items concerning experiences with mother as a trustworthy source for support (e.g., “I can count on my mother to help me when I have a problem”). Children have to indicate how true the item is for them on a Likert scale ranging from 1 (almost never true) to 4 (almost always true). We administer the subscale before intervention to determine baseline trust in maternal support. Shortly after intervention we readministered the scale to allow assessment of change in trust. The PIML is a valid self-reported measure for middle childhood [14] and has been used in previous research to assess change in trust in maternal support [23].

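### The change-score ANOVA omits the pre-intervention value as a covariate; the analysis is valid, but adding it would cost one degree of freedom and could gain precision

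*Protocol article*

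**What the plan says.** The effect model is stated in Data analysis: "To assess the main and interaction effects of the interventions on change scores on these outcome measures, we will perform a two-way ANOVA". Its only two factors are training and spray, and no baseline term is included. Table 2 under Outcome measures defines five of its six outcomes as change. For both interpretation bias ratings, for example, the metric is "Change from pre-intervention to post-intervention recognition task". The pre-values are therefore in hand; for trust the article says "We administer the subscale before intervention to determine baseline trust in maternal support".

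Beyond the subtraction, the pre-values have one further use: "We use one-way analyses of variance (ANOVAs) to assess pre-intervention differences between the four intervention conditions on the outcome measures". No consequence for the effect model is attached to the result. The only covariate named in Data analysis belongs to the oxytocin dose check: "OT dose (12 IU versus 24 IU) as between-subject variables and children’s weight as covariate". The Mood section allows for control of mood effects, but not for the starting level of the outcome itself.

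**The concern.** A change score is an adjusted post score whose baseline slope has been set to 1 in advance. The slope in the data is r × SDpost/SDpre, and nothing in the article suggests that it equals 1 for all five outcomes. Where it does not, two things follow. The residual variance is larger than the same data allow. In addition, part of any chance difference between groups at baseline remains in the estimated effect.

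The baseline ANOVAs do not address either point, because testing a difference does not remove it. Precision matters here: the Sample size section powers the trial for f = 0.30 but also cites an overall oxytocin effect of f = 0.24 from a meta-analysis, and all the pre-values needed for a better model are already being collected.

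**Working it through.** **Inputs.** From Sample size: "moderate effect size, *f* = 0.30"; "alpha = .05, two-tailed; power = 0.80"; numerator df 1; four groups; 100 children, 25 per cell, hence 50 v 50 for each main effect. The article gives neither r nor any standard deviation, so r is varied from 0.3 to 0.9 as an assumption.

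**Step 1: the plan's own figure.** Noncentral F with λ = f²N, df1 = 1, df2 = N − 4.
- N = 90: λ = 0.09 × 90 = 8.1, critical F = 3.952, power 0.803. At N = 89 power is 0.799, so 90 is the smallest adequate N.
- N = 100: λ = 9, critical F = 3.940, power 0.844.

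Both agree with the stated 90 (0.80) and 100 (0.84).

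**Step 2: variance under the two models.**
- Var(change) = SDpre² + SDpost² − 2r·SDpre·SDpost
- Var(ANCOVA) = SDpost²(1 − r²)
- Difference = (SDpre − r·SDpost)² = SDpre²(1 − slope)², with slope = r·SDpost/SDpre

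The difference is never negative, and it is zero only when the slope is 1. Example of no gain: r = 0.8, SDpost/SDpre = 1.25, slope = 1. Then Var(change) = 1 + 1.5625 − 2 = 0.5625 and Var(ANCOVA) = 1.5625 × 0.36 = 0.5625.

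**Step 3: size with equal SDs.** The variance ratio ANCOVA/change is (1 − r²)/(2(1 − r)) = (1 + r)/2. With f = 0.30 on the change scale, f for ANCOVA is 0.30 × √(2/(1 + r)), and df2 = N − 5 = 95 at N = 100.

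| r | Variance ratio | f (ANCOVA) | Power, N = 100 | N for power 0.80 | 100 children equal, by change score |
|---|---|---|---|---|---|
| 0.3 | 0.65 | 0.372 | 0.958 | 59 | 154 |
| 0.5 | 0.75 | 0.346 | 0.929 | 68 | 133 |
| 0.7 | 0.85 | 0.325 | 0.896 | 77 | 118 |
| 0.8 | 0.90 | 0.316 | 0.879 | 81 | 111 |
| 0.9 | 0.95 | 0.308 | 0.861 | 85 | 105 |

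The comparators for the change-score ANOVA are power 0.844 and N = 90. Simulation (20,000 trials each) gave power 0.846 v 0.929 at r = 0.5, 0.848 v 0.899 at r = 0.7 and 0.843 v 0.875 at r = 0.8 (change score v ANCOVA).

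The article does not say on which scale f = 0.30 is defined. If it refers to the post-score SD, power is 0.709 v 0.876 at r = 0.3 and 0.844 v 0.929 at r = 0.5, and the two models nearly coincide at r = 0.8 (0.997 v 0.999).

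**Step 4: baseline imbalance.** For 50 v 50, the baseline difference has SE √(2/50) = 0.20 SD. The change-score estimate moves by (slope − 1) times the observed difference. With equal SDs:
- r = 0.5: a 1-SE difference shifts the estimate by 0.5 × 0.20 = 0.10 SD, and a 1.96-SE difference by 0.5 × 0.392 = 0.20 SD.
- r = 0.8: 0.04 SD and 0.08 SD.

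In the simulations the change-score estimate moved with the imbalance at slopes of −0.50, −0.29 and −0.20 for r = 0.5, 0.7 and 0.8; the ANCOVA slope was about 0. Averaged over all trials, both estimators recovered the true effect.

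**The case against.** The plan is coherent: hypotheses, outcome definitions and analysis are largely framed as change. The power statement reproduces and exceeds its target of 0.80. No contradiction or type I error problem is shown. All of that stands.

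Several stronger readings are tempting, but the article does not support them.
- A reader might infer that the effect estimates are biased. Under random allocation they are unbiased on average; the shift in Step 4 is conditional on the imbalance that happens to occur, and only the fraction (1 − slope) of that imbalance enters.
- A reader might infer that any correlation below 1 guarantees a gain. It does not: the slope decides, and Step 2 shows a case with r = 0.8 and no gain.
- A reader might say that baseline is ignored apart from a significance test. It is also subtracted in every change score, which is itself an adjustment.
- A reader might dismiss the baseline comparison as pointless in a randomised trial. According to Study design, only the spray is randomised; training condition is alternated between consecutive participants, and experimenters know it. Showing comparability on that factor therefore has a purpose.

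The gain may also be modest. Pre and post measures fall within one session of 120 to 150 minutes, and trust uses the same ten items twice, so r could be high. At r = 0.8 to 0.9 with equal SDs, the gain is 1.7 to 3.5 percentage points of power. Finally, a linear covariate does not remove a ceiling on the 1-to-4 rating scales.

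**Conclusion.** The point holds as an improvement in efficiency and in protection against chance imbalance, not as the correction of an error. The planned model imposes a slope of 1 that the article does not justify, and leaves out a covariate that is already collected for five outcomes. The size of the gain is unknown. With equal SDs and f = 0.30 on the change scale, it runs from about 11 percentage points of power at r = 0.3 (0.958 − 0.844) to about 2 at r = 0.9 (0.861 − 0.844). With unequal SDs it can be nil. Apart from the one degree of freedom, the covariate model has residual variance no larger than that of the change score. The sample size calculation is right for the model it describes. Unbiasedness on average rests on randomisation for the spray; for training it rests on alternation acting like random allocation.

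**What to change.** Before unblinding, state in the analysis plan that each outcome with a pre-measure is analysed with training, nasal spray, their interaction and the pre-intervention value of that same outcome as covariate. Using the post value or the change score as the response gives the same effect estimate. Apply this model whatever the baseline comparison shows, so that the baseline ANOVAs do not decide on adjustment, and report baseline values descriptively by group. Keep that display for the training factor in particular, since its allocation is alternated. Leave interpretation speed as planned.

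The cost is one sentence and one degree of freedom, with no new data. The change is still open: Trial status says that recruitment continues, and under Study design the envelopes stay sealed until data collection ends, except for emergency unblinding.

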### Interventions

#### OT intervention

The pharmacy of the University Hospital of Heidelberg, Germany prepares the study medication. Half of the participants receives OT (Syntocinon®, 40 international units (IU)/ml), the other half receives PL (0.9% sodium chloride solution). The bottles containing OT and PL are identical: 10-ml brown glass bottles, hydrolytic class type III, with DIN ND 18 screw thread. The nasal pump has a volume of 0.05 ml per puff. We weigh children on a digital personal scale and base the amount of nasal spray administered on the child’s weight. The conventional dose in adult studies is 24 IU OT, although a study comparing different doses in adults has shown that salivary OT levels were equally elevated after intranasal administration of 24 IU OT and of 16 IU OT [51]. Studies involving OT nasal spray in children (under 12 years) used doses varying between 8 IU and 24 IU. These studies based the amount of nasal spray administered on age as a proxy for weight [24], on weight [36], or gave all children the same (stepwise raised) amount of OT [39]. These studies either found that the results did not depend on OT dosage [36, 39] or did not report on dosage effects [24]. As it is most common to base drug doses in pediatric populations on weight [52], we used the same weight-based dosing strategy as in the study by Dadds et al. [36]: children weighing less than 40 kg receive 0.3 ml nasal spray (i.e., 12 IU OT for the OT condition); children weighing more than 40 kg receive 0.6 ml (i.e., 24 IU OT for the OT condition). Single administration of OT in dosage amounts up to 40 IU has not resulted in side-effects or adverse outcomes [53].

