We based the nasal spray administration procedure on recommendations by Guastella et al. [54]. Before use, the experimenter primes the spray by pumping approximately seven to eight times until a fine mist is visibly released. After priming, the experimenter weighs the bottle on an apothecary scale (Kern EMB 200-2). Experimenters ask the children to keep their head upright or slightly tilted backwards during administration. Experimenters explain to the children that we will alternate administration between nostrils and that they have to keep the other nostril closed with one finger and inhale lightly two or three times upon nasal spray delivery. Child and experimenter practice this administration procedure together before actual administration. Either the experimenter, or the child itself under experimenter supervision, administers the spray. Experimenters make sure that the top of the nasal spray is inserted into the nose about 1 cm and that the bottle is held at a slight angle such that the pipe is well immersed in the fluid at all times. After 6 (for children under 40 kg) or 12 (for children over 40 kg) pumps, the experimenter weighs the spray again on the scale. If necessary, we administer extra pumps until at least 0.26 ml or 0.56 ml has been released from the bottle. Experimenters register the amount of nasal spray administered.

Subsequently, children wait for 35 min, during which they can choose to draw, read a comic or watch a video. During the break, experimenters make sure that children remain calm (e.g., do not watch exciting videos), do not eat or drink except for water, and are not in contact with their mother.

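### The oxytocin-only dose check contrasts heavier with lighter children; without the placebo children it does not measure whether the oxytocin effect differs by dose

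*Protocol article*

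**What the plan says.** The protocol article gives the aim in Data analysis: "in order to check whether the dose of intranasal OT that is administered affects intervention effects on change scores on the outcome measures". The check is confined to children who received oxytocin and has training as its first factor; the second factor and the adjustment are "OT dose (12 IU versus 24 IU) as between-subject variables and children’s weight as covariate". Placebo children do not enter it.

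The OT intervention section says how dose arises. The investigators "base the amount of nasal spray administered on the child’s weight": "children weighing less than 40 kg receive 0.3 ml nasal spray (i.e., 12 IU OT for the OT condition"), and "children weighing more than 40 kg receive 0.6 ml (i.e., 24 IU OT for the OT condition"). The volume rule is written for the spray as such, and the IU figure is added for the oxytocin condition, so placebo children are split into the same two weight bands. The bands also differ in the number of sprays: "After 6 (for children under 40 kg) or 12 (for children over 40 kg) pumps, the experimenter weighs the spray again on the scale".

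**The concern.** An intervention effect of oxytocin is a contrast of oxytocin with placebo. To ask whether dose changes that effect is to ask whether the contrast differs between the two weight bands. The planned model holds one side of the contrast only, so its dose term cannot be told apart from anything else that differs between children under and over 40 kg: weight, age, puberty, spray volume, number of puffs.

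The weight covariate helps only in part. No two children of equal weight have different nominal doses, so with weight in the model the dose coefficient is a jump at 40 kg measured against a straight line. It is a dose effect only if the line is truly straight and nothing else jumps there. The training × dose term is better placed, because neutral training is a comparator for the CBM effect under oxytocin. It is still confounded with weight band, as no training × weight term is planned.

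At stake is a false dose finding, a masked one, or a null that carries very little information.

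**Working it through.** **The plan's own figure.** The article gives no precision for the dose check. Its main sample size reproduces. With f = 0.30, 1 and N − 4 degrees of freedom and noncentrality f²N:
- N = 90: 0.09 × 90 = 8.1, critical F 3.95, power 0.803.
- N = 100: 0.09 × 100 = 9.0, critical F 3.94, power 0.844.

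With two equal groups, f = 0.30 is a difference of 0.6 SD, used below as the yardstick.

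**Inputs for the dose check.** Half of 100 children receive oxytocin, so n = 50. The cut is 40 kg. The article gives no weight distribution. I assume normal weights with mean 38 and SD 8 kg, and vary this from 32/6 to 42/9 kg. Residual SD is set to 1.

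**Precision of the planned model.**
- Share above 40 kg: p = 1 − Φ((40 − 38)/8) = 0.401, so p(1 − p) = 0.240.
- Squared dose–weight correlation: φ(0.25)²/[p(1 − p)] = 0.3867²/0.240 = 0.622.
- Variance inflation: 1/(1 − 0.622) = 2.65.
- SE of the dose effect: √(2.65/(50 × 0.240)) = 0.47 SD.
- Power for 0.6 SD: 0.24 by formula, 0.21 to 0.22 in simulation; about 0.23.

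Over the assumed weight distributions, 9% to 59% of children exceed 40 kg, variance inflation is 1.5 to 2.75, power is 0.17 to 0.24, and the difference detectable with 80% power is 1.34 to 1.71 SD.

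**Precision with the placebo arm.** The SE of spray × band on all 100 children is √(2/(50 × 0.240)) = 0.41 SD by formula and 0.42 in simulation; simulated power for 0.6 SD is about 0.29. Adding a spray × weight term multiplies the variance by 2.65: √(2 × 2.65/(50 × 0.240)) = 0.66 by formula, about 0.69 in simulation. Training × spray × band has an SE of about 0.84, and power near 0.11 for 0.6 SD.

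**What each model estimates.** Simulation with 4,000 trials per row and mean 38, SD 8 kg. Cells give the mean estimate in SD units and the rejection rate at 5%. The weight effects are assumptions chosen to show the mechanism.

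| True state | Planned, oxytocin only | Spray × band, all 100 |
|---|---|---|
| Linear weight trend, no oxytocin effect | about 0; 5% | about 0; 5% |
| 0.6 SD step at 40 kg in both arms, no oxytocin effect | 0.60; 23% | −0.01; 5% |
| S-shaped weight trend in both arms, no oxytocin effect | 0.45; 14% | 0.01; 5% |
| Quadratic weight trend in both arms, no oxytocin effect | 0.24 to 0.31; 10% to 11% | about 0; 5% |
| Oxytocin effect 0.6 SD at 24 IU only | 0.59; 21% | 0.59; 29% |
| The same, offset by a −0.6 SD step in both arms | 0.01; 5% | 0.60; 29% |
| Oxytocin effect 0.6 SD at both doses | 0.00; 5% | 0.01; 5% |
| Oxytocin effect rising 0.3 SD per SD of weight, no dose step | about 0; 5% | 0.48; 20% |

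The range in the quadratic row depends on whether extreme weights are truncated. The planned model returns zero both when oxytocin does nothing and when it works equally at both doses, because it never estimates the oxytocin effect. The last row shows where the planned model does better.

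**The case against.** Several points for the plan stand.

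- A reader might infer that the check is uninterpretable because dose and weight are collinear. They are not: a step and a straight line can be separated (variance inflation 1.5 to 2.75), and under a linear weight trend the planned model rejects at the nominal 5%.
- A reader might infer that any curvature in the weight trend produces a false dose effect. It does not: with mean weight 40 kg, a symmetric quadratic trend gives an estimate of about 0.01. The bias depends on the shape, and nothing in the article shows that a 0.6 SD jump at 40 kg is likely in a change score measured within one session.
- A reader might infer that spray × band is a clean dose test. It is not. If the oxytocin effect itself rises with weight, it gives a false signal of 0.48 SD where the planned model gives none.
- The training × dose term does have a comparator, and it bears on the hypothesis that oxytocin enhances CBM.
- The article does not say how a null result would be read, so a claim that dose will be declared irrelevant would be conjecture.

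What does not fall is the mismatch between aim and model. The aim is the effect of dose on intervention effects; the dose main effect in an oxytocin-only model contains no oxytocin-versus-placebo contrast, while placebo children in both bands are available. The low-power caveat in the Discussion concerns participant moderators, not this check.

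**Conclusion.** The point holds in limited form. The dose main effect as planned is a comparison of heavier with lighter children, and becomes a dose effect only with a linear weight trend and no other change at 40 kg. Volume and number of puffs do change there, and only the placebo arm can account for them. Under the assumed weights, a shared 0.6 SD step passes into the dose estimate in full, and power for a true 0.6 SD difference is about 0.23. Adding the placebo arm removes shared steps and trends and raises power to about 0.29, which is still low. Neither model can separate dose from weight and age as modifiers of the oxytocin effect.

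This is a supplementary check. The randomised 2 × 2 comparisons and the sample size do not depend on it, and a reader should not carry the weakness over to them. The size of any bias rests on assumed weights and assumed trends; the article gives neither.

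**What to change.** 1. Add a model on all 100 children with training × spray × weight band (below or above 40 kg) and weight as covariate. Make spray × band the main dose check, and report the oxytocin-minus-placebo difference in each band with its confidence interval. Treat the three-way term as descriptive, given its SE of about 0.84 SD.
2. Keep the planned oxytocin-only model as a sensitivity analysis, or use a spray × weight term for that purpose. The latter protects against an oxytocin effect that changes linearly with weight, but widens the SE from about 0.42 to about 0.69 SD.
3. Label the check exploratory. State that a difference between bands reflects dose together with weight and age, and that non-significance is not evidence that dose is irrelevant.

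Whether to adjust for the pre-intervention outcome is a separate question and is not part of this change. The cost is analysis wording only: children are weighed to set the volume and the amount sprayed is registered, so no new data are needed. Nothing here bears on which dose children should receive.
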